### Risks to participants from the intervention

The risk relating to the intervention is minimised as patients who are not suitable to undertake exercise are excluded, and participants will not be asked to undertake exercise beyond their physical ability. The exercise sessions will be delivered by trained physiotherapists who will work closely with the ICU clinical team, and they will have frequent contact and access to the ICU team for any queries that may arise. The records and baseline assessment of all participants included in the study will be reviewed by an ICU physician.

### Researcher safety

On occasions when home visits are required the researchers will follow the research group safety protocol for home visits. When scheduling the home visit the researcher will conduct a preliminary risk assessment. Prior to the home visit they will complete an offsite visit itinerary form, including a nominated contact person’s details and a call schedule. The contact person will be another member of the research team available during the visit.

### Data collection

Blinded outcome assessment will be conducted at baseline within two weeks of hospital discharge or when the patient is deemed medically stable (or in exceptional circumstances this will take place immediately prior to hospital discharge), following the exercise intervention, and at 6 months (24 weeks) following baseline assessment (or equivalent time points for the standard care group). These will be conducted by trained independent assessors blinded to group allocation. Informed consent will be obtained from each participant. Following consent and randomisation, the following will be recorded: demographics, ICU diagnosis and any co-morbidity and illness severity using acute physiology and chronic health evaluation II score.

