### Recruitment

Patients in the ICUs will be prospectively screened. All eligible consecutive patients will be given written information about the study following discharge from critical care. They will be approached to enquire if they are interested and willing to take part in the study. A screening log of all non-recruited patients and the reason for exclusion will be maintained. If willing to participate, patients will be asked to provide written informed consent by a trained member of the research team prior to commencing the study. Participants will be randomised to the exercise programme or standard care. A randomisation schedule will be produced using permuted block randomisation technique, at a 1:1 ratio. Variable block sizes are used to ensure blinding. The randomisation schedule will be generated using nQuery Advisor by the clinical trials unit (NICTU). Allocations are done centrally by the NICTU (allocation concealment). The randomisation service will allocate a unique trial identification number to each participant in accordance with the computer-generated study randomisation schedule. In order to maintain confidentiality, all case report forms, study reports and all communication regarding the study will identify participants using the unique identification numbers. Participants allocated to the programme of exercise will commence as soon as possible.

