### Sample size

There is limited data available in this specific research area in order to conduct a formal sample size calculation. Jones and colleagues [11] demonstrated an approximate 24% improvement in the physical function score of the SF-36 with a rehabilitation manual which included a self-directed exercise programme. With the limited data available we have used a more general method to calculate the sample size [18], which would result in 52 patients (26 per group) for a large effect size. On the basis of our previous experience and published data we have estimated a loss of 25% after randomisation [19]. Thus, this study will aim to recruit up to 68 patients (34 in each group), or until we achieve 52 (26 per group) completed datasets at 6 weeks over the proposed 36-month recruitment period. Participants will be withdrawn on request, if there are adverse effects arising from the exercise programme, or due to inability to perform baseline assessment.

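### The protocol implies, without stating it, that allocation comes before the baseline assessment; withdrawing patients who cannot do baseline then conflicts with intention to treat

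*Protocol article*

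**What the plan says.** All references are to the protocol article.

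- **Recruitment.** Consent is described first ("patients will be asked to provide written informed consent by a trained member of the research team prior to commencing the study"). Randomisation and central allocation follow, with no baseline step in between. The randomisation service issues the trial number, and every case report form carries that number. Then: "Participants allocated to the programme of exercise will commence as soon as possible".
- **Data collection.** "Blinded outcome assessment will be conducted at baseline within two weeks of hospital discharge or when the patient is deemed medically stable". Of the assessments at all time points, baseline included: "These will be conducted by trained independent assessors blinded to group allocation". On patient characteristics: "Following consent and randomisation, the following will be recorded: demographics, ICU diagnosis and any co-morbidity and illness severity".
- **Sample size.** "we have estimated a loss of 25% after randomisation". The same paragraph lists the reasons for withdrawing participants, ending with "or due to inability to perform baseline assessment". Recruitment runs to at most 68, or until 52 complete six-week datasets exist.
- **Statistical methods/analyses.** Efficacy is to be analysed by intention to treat. Analysis of covariance is among the methods, and baseline imbalance may trigger post-hoc adjustment. Missing baseline and outcome data will be examined and, if necessary, handled by multiple imputation or Bayesian methods.

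**The concern.** Baseline is usually measured before allocation for two reasons: a patient who cannot complete it is then a screening failure rather than a lost randomised patient, and the baseline value cannot be affected by the arm. The order implied here gives up both protections.

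First, a patient can be randomised, fail baseline and be withdrawn. Patients facing an exercise programme and patients facing no extra care may differ in whether they reach and complete baseline, so the loss can depend on arm. Recruiting on until 52 datasets are complete restores the number but not the balance that randomisation gave.

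Second, the primary outcome is a self-reported SF-36 subscale, and the EQ-5D is self-reported too. Blinding is described for assessors and the statistician, not for participants. A baseline answered by someone who knows the arm is a doubtful basis for comparability checks and for adjustment.

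The wait for medical stability has no upper limit. In patients recovering from more than 96 hours of ventilation, it lengthens the interval in which either problem can arise.

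**Working it through.** **1. The protocol's own figures.** The article gives no numerical effect size or power. Assuming d = 0.8 for a large effect, two-sided alpha 0.05 and 80% power, the two-sample t-test needs 25.5 per group. Rounded up, this is 26 per group or 52 in all, as stated; power at 26 per group is 80.7%. For the loss, 68 × 0.75 = 51 completers, one short of 52. These figures neither support nor refute the point about order.

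**2. The order of events.** Each statement is tested against both orders.

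| Statement | Allocation first | Baseline first |
|---|---|---|
| Consent, then randomisation, no baseline step between (Recruitment) | fits | baseline step omitted |
| Trial number issued by the randomisation service and used on all case report forms (Recruitment) | fits | baseline form would have no number |
| Assessors blinded to allocation, baseline included (Data collection) | fits | nothing to be blinded to at baseline |
| Characteristics recorded after randomisation (Data collection) | fits | possible, since the list omits SF-36 and EQ-5D |
| Participants withdrawn for inability to do baseline (Sample size) | fits | would be a screening failure |
| Exercise starts as soon as possible after allocation (Recruitment) | fits | fits |

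No statement places baseline before allocation. The order is therefore a strong inference, resting mainly on the trial number, the assessor blinding and the withdrawal reason.

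**3. Size of an arm-dependent loss (assumed rates).** Suppose one arm alone loses the lowest fraction q of baseline scores, normally distributed. Its baseline mean rises by φ(z_q)/(1 − q) SD, and its follow-up mean by that amount times the baseline–outcome correlation, assumed to be 0.5.

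- q = 0.05: rise 0.109 SD; follow-up shift 0.5 × 0.109 = 0.05 SD
- q = 0.10: rise 0.195 SD; follow-up shift 0.10 SD
- q = 0.25: rise 0.424 SD; follow-up shift 0.21 SD

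This applies to an unadjusted comparison, which the article allows. Adjustment for baseline would remove the part that depends on the baseline score alone, but not loss for other reasons.

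**4. Size of an allocation-influenced baseline (assumed shifts).** In analysis of covariance the estimate is (difference in outcome) − b × (difference in baseline). A reporting shift s in one arm's baseline therefore moves the estimate by b × s.

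- b = 0.3, s = 0.1 SD: 0.03 SD
- b = 0.5, s = 0.2 SD: 0.10 SD
- b = 0.7, s = 0.3 SD: 0.21 SD

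The direction depends on which arm shifts and which way. Against the assumed effect of 0.8 SD, the range runs from 0.03/0.8 = 4% to 0.21/0.8 = 26%.

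**The case against.** The strongest reply is that the order is inferred. The sentence about recording after randomisation lists demographics, diagnosis, co-morbidity and severity, which knowledge of the arm can hardly bias; it does not mention the SF-36 or EQ-5D. The blinding statement covers all time points together, and the flow diagram, which might settle the sequence, is not available here. This stands, and is why the point is worded as an implication.

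Next, withdrawn need not mean excluded from analysis. The statistical section allows for imputation and undertakes to pursue outcomes even in people who leave the exercise programme. This also stands in part, but that undertaking does not clearly reach someone withdrawn before baseline, and the article does not say how such a person enters the intention-to-treat analysis.

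A reader might go further in three ways, none of which the text supports:

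- That the physician's review removes randomised patients. The article says only "The records and baseline assessment of all participants included in the study will be reviewed by an ICU physician", under risk minimisation, and attaches no exclusion to it.
- That a known share of the 25% loss comes from failed baselines, so that reordering would save patients. The article attributes none of the loss to this cause. Reordering also moves such failures ahead of allocation without reducing the number of people to be approached.
- That the QALY analysis is compromised through baseline adjustment. The health economic section specifies no such adjustment.

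Finally, the trial has been randomising since January 2012 at what are now five sites, so a change of order gives two differently selected groups of patients within a small trial. That is a real cost, but it can be reported and examined.

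**Conclusion.** The point holds as an implied order that the protocol should settle. On the most natural reading, allocation precedes baseline. The withdrawal reason then sits badly with intention to treat, and the self-reported baseline may be given with knowledge of the arm. That any participant has actually been dropped from analysis, or knew the arm at baseline, is not documented; the article does not say when participants learn their allocation.

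The size cannot be fixed from the documents. The illustrative range of about 0.03 to 0.21 SD rests on the assumed one-arm loss of 5–25%, correlation of 0.5, reporting shift of 0.1–0.3 SD and covariate slope of 0.3–0.7. Its upper end matters beside an assumed target of 0.8 SD; its lower end does not. If baseline does in fact come first, the bias concern falls away and only the wording needs correcting.

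**What to change.** State the order of consent, baseline and allocation explicitly.

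- **Not yet randomised:** complete the baseline assessment before requesting the central allocation. Inability to perform baseline then becomes an exclusion before randomisation; delete it from the withdrawal reasons under Sample size.
- **Already randomised without a baseline:** keep them in the intention-to-treat set, follow them for outcomes, and impute the missing baseline under the existing missing-data provision.
- **Trial number:** since it now comes from the randomisation service, arrange an identifier for baseline forms completed before allocation.
- **If baseline already comes first:** say so, and correct Sample size and Data collection to match.

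The cost is a protocol amendment, a change in when sites call the service, later booking of exercise sessions, and a mid-trial change of order whose date and the numbers randomised under each order must be reported. No extra visit is needed.

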### Outcome measures

The primary outcome measure is physical function as measured by the physical functioning subscale of the SF-36 following the exercise programme. This has been shown to be an acceptable, reliable and valid tool following critical illness [25].

Several secondary outcomes will be evaluated to determine whether an exercise programme can improve these important clinical outcomes. These outcome measures will assess physical function, health-related quality of life, exercise capacity, anxiety and depression and self-efficacy to exercise in these participants. Healthcare resource use will also be evaluated [25-35] (Table 1).

**Table 1 T1:** Secondary outcome measures

**Outcome measure**	**Instrument**
Physical function	Rivermead Mobility Index [26]
Hand function (strength and dexterity)	Dynamometry [27]
	Nine Hole Peg Test [28]
Exercise capacity	Incremental Shuttle Walk Test [29]
Health-related quality of life	Other subscales of the Short-Form-36 Health Survey (role limitations due to physical health, bodily pain, general health perceptions, vitality, social functioning, role limitations due to emotional problems, and mental health) [25]
	Functional Limitations Profile [30]
	EuroQol 5 dimension questionnaire 5 level version [31]
Breathlessness	Medical Research Council Dyspnoea Scale [32]
Anxiety and depression	Hospital Anxiety and Depression Scale [33]
Readiness to exercise	Readiness to Change Questionnaire [34]
Self efficacy to exercise	Chronic Disease Self Efficacy Scale [35]
Healthcare resource use	Resource use questionnaire

Feasibility (safety, practicality and acceptability) of providing the exercise programme will also be assessed by the occurrence of adverse events, and recording information relating to recruitment and retention, and any difficulties with attendance and transport. Information regarding ease of execution of the exercise programme and the outcome measures will also be recorded.

In addition, we will conduct semi-structured interviews to explore participant’s perceptions of the exercise programme. On completion of the exercise programme semi-structured interviews will be used to explore participant satisfaction, views about continuing exercise and suggestions for improving the exercise programme. A list of clear, open-ended questions will be prepared by the research team [36]. The interviews will be carried out by a trained researcher not involved in the delivery of the intervention or blinded outcome assessment. All interviews will be audio taped, transcribed and analysed. Finally, the results from this qualitative component, along with the results from the outcome measures from the trial, will provide greater insight into both the process and effects of the intervention.

### Statistical methods/analyses

For continuously distributed outcomes, differences between groups will be tested using independent samples *t*-tests, analysis of variance and analysis of covariance with transformations of variables to normality if appropriate, or non-parametric equivalents. Chi-square tests (or Fisher’s Exact tests) will be used for categorical variables. Efficacy of intervention will be analysed on an intention-to-treat basis. A *P* value ≤0.05 will be considered significant. A single final analysis is planned at the end of the trial. Baseline variables will be recorded to demonstrate that the groups are comparable; if this is not demonstrated, *post-hoc* adjustments to correct for differences will be applied. Every effort will be made to collect outcomes from patients, even those who drop out of the exercise programme. Every effort will be made to minimise missing baseline and outcome data in this trial. The level and pattern of the missing data in the baseline variables and outcomes will be established by forming appropriate tables and the likely causes of any missingness will be investigated. This information will be used to determine whether the level and type of missing data has the potential to introduce bias into the analysis results for the proposed statistical methods, or substantially reduce the precision of estimates related to treatment effects. If necessary, these issues will be dealt with using multiple imputation or Bayesian methods for missing data as appropriate. The power calculations and methodology for data analysis have been reviewed and confirmed by the study statistician. Until data analysis is completed the study statistician will be unaware of whether the participant received the intervention or standard care.

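### Baseline adjustment hangs on an undefined comparability check; the main cost is lost precision and power, which a prespecified ANCOVA would recover almost free

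*Protocol article*

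**What the plan says.** Under Statistical methods/analyses, the protocol article offers independent-samples t-tests, "analysis of variance and analysis of covariance with transformations of variables to normality if appropriate, or non-parametric equivalents" for continuous outcomes in general. No test is assigned to the primary outcome and no ANCOVA covariate is named. On baseline data it says: "Baseline variables will be recorded to demonstrate that the groups are comparable; if this is not demonstrated". In that event, and under the label post-hoc, the article promises that "adjustments to correct for differences will be applied". A P "value ≤0.05 will be considered significant". The same section keeps the study statistician unaware of allocation until the analysis is finished.

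The Sample size section arrives at a number "which would result in 52 patients (26 per group) for a large effect size". The Data collection section places an outcome assessment at baseline. The primary instrument, SF-36 physical functioning, should therefore be available as a covariate.

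**The concern.** Allocation is central, concealed and random at 1:1, so there is no comparability to demonstrate: any baseline difference is chance. Adjustment is worth making when a covariate predicts the outcome, because it then removes outcome variance whether or not the groups look balanced. The stated rule works the other way round. It leaves a strongly prognostic covariate unused when balance looks acceptable, and brings one in after the data are seen when it does not.

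Three things are at stake:

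- precision and power, in a trial sized only for a large effect;
- the identity of the primary estimator, which may be adjusted or unadjusted depending on chance;
- the freedom left by a trigger with no criterion and no covariate list.

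**Working it through.** **Inputs from the protocol article.** 26 evaluable participants per group; significance at 0.05; 1:1 allocation; a conditional rule with no threshold.

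**Assumptions, because the article gives no figure.** Two-sided testing; large effect taken as d = 0.8; 80% power; one covariate (the baseline score); comparability judged by a baseline t-test at 0.05; baseline-outcome correlation ρ of 0.3, 0.5 or 0.7.

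**1. The plan's own figure.** n per group = 2(1.96 + 0.842)²/0.8² = 24.5, so 25 by the normal approximation. With the noncentral t distribution, power is 0.791 at 25 per group and 0.807 at 26. The stated 52 (26 per group) is reproduced under these assumptions.

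**2. How much imbalance escapes a 0.05 trigger.** The critical baseline difference is t(0.975, 50) × √(2/26) = 0.557 SD. About 95% of trials stay unadjusted. The share s of the variance of the chance imbalance left uncorrected is about 0.73 in simulation. It depends on the threshold: by normal theory, s = (2Φ(c) − 1) − 2cφ(c), which is about 0.56 for a 0.10 trigger and 0.35 for a 0.20 trigger.

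**3. Precision.** In units of the outcome SD, the estimator variance is approximately:

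- unadjusted: 2/n, so SD = √(2/26) = 0.277;
- conditional rule: (2/n)[1 − ρ²(1 − s)];
- ANCOVA always: (2/n)(1 − ρ²), plus a little for estimating the slope.

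At ρ = 0.5 and s = 0.73, the rule gives √(0.0769 × 0.9325) = 0.268. ANCOVA gives √(0.0769 × 0.75) = 0.240 before the slope term.

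**4. Simulation.** 400,000 trials per setting, 26 per group. Power is at d = 0.8; the other columns are under the null.

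| ρ | SD, rule | SD, ANCOVA always | Power, rule | Power, ANCOVA always | Type I, rule | Type I, ANCOVA always |
|---|---|---|---|---|---|---|
| 0.3 | 0.274 | 0.267 | 0.809 | 0.835 | 0.047 | 0.049 |
| 0.5 | 0.268 | 0.243 | 0.816 | 0.898 | 0.043 | 0.050 |
| 0.7 | 0.259 | 0.200 | 0.825 | 0.975 | 0.036 | 0.050 |

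The variance ratio, rule to ANCOVA, is (0.2741/0.2666)² = 1.06, (0.2683/0.2430)² = 1.22 and (0.2590/0.2002)² = 1.67. A plain t-test has power of about 0.807, so the rule gains almost nothing over never adjusting.

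**5. Where the error rate does rise.**

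- Among null trials with a baseline P between 0.05 and 0.20, which stay unadjusted, type I error is 0.062, 0.086 and 0.116. ANCOVA gives 0.048 to 0.050 in the same trials.
- If either the adjusted or the unadjusted result could be reported, type I error is 0.063, 0.073 and 0.083.

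**6. Dependence on how many variables are inspected.** With 5 or 10 independent variables, each tested at 0.05, the chance of at least one apparent imbalance is 1 − 0.95⁵ = 23% or 1 − 0.95¹⁰ = 40%, although allocation is random.

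**The case against.** The strongest reply is that the rule does little damage. Applied as modelled, it is conservative, unbiased over repeated randomisations, slightly more precise than a plain t-test, and still above the assumed 80% power. All of that stands. The harm is mainly efficiency forgone.

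Two stronger readings are tempting, and the documents support neither:

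- **The rule inflates the false-positive rate.** Overall it falls below 5%. Inflation is confined to trials with moderate unadjusted imbalance, or to a free choice of analysis, which the article leaves open but does not say will be made.
- **The rule biases the result.** Unflagged imbalance above 0.4 SD shifts the estimate by 0.14, 0.23 or 0.33 SD on average in size (ρ = 0.3, 0.5, 0.7). But that concerns about 10% of trials, and either direction is equally likely.

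It can also be said that ANCOVA is already listed, that covariate choice is commonly left to an analysis plan not shown here, and that the statistician is blinded. The first means that adjustment is not strictly confined to the trigger. The second means that a missing covariate list is not in itself a fault. Neither cures a sentence that positively makes adjustment depend on observed imbalance and calls it post-hoc: a later plan could only follow it or contradict it. Blinding limits steering towards an arm, but it does not define the trigger in advance or recover the lost precision.

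Finally, the article does not say that a significance test will judge comparability. A looser or clinical judgement would leave less imbalance uncorrected, but at any test threshold up to 0.20 at least 80% of trials stay unadjusted.

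**Conclusion.** The point holds as a weakness of efficiency and prespecification, and should be fixed. It does not show that the trial's primary test would be invalid. Under the stated assumptions the rule gives up about 3, 8 and 15 percentage points of power (0.835 − 0.809, 0.898 − 0.816, 0.975 − 0.825) at correlations of 0.3, 0.5 and 0.7. It also leaves open which estimator is primary.

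The sizes rest on an assumed trigger of 0.05, d = 0.8, a single covariate and assumed correlations. At a low correlation the loss is small. The claim that most chance imbalance stays uncorrected depends on the threshold: about 73% of its variance at 0.05, but about 35% at 0.20. The calculation also takes the baseline score to be unaffected by allocation.

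**What to change.** Delete the conditional sentence. Before unblinding, state that the primary analysis is an ANCOVA of post-programme SF-36 physical functioning with the baseline score as covariate, whatever balance is seen. One or two prognostic variables already collected, such as age or the APACHE II score, may be added if named at the same time. Present baseline data descriptively by group. Label any further adjustment prompted by observed imbalance as a sensitivity analysis.

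The cost is a sentence or two of text and one to three degrees of freedom. No new data and no extra participants are needed.
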